**Medical Contact on site:**

The medical site manager, [contact] [name]

Study Synopsis

| Title of clinical trial | A Universal Form of Treatment Options (UFTO): A study to evaluate the UFTO as an alternative to the DNACPR |
| --- | --- |
| Sponsor name | Addenbrooke’s Hospital |
| Medical condition or disease under investigation | All medical conditions |
| Purpose of clinical trial | To assess the UFTO as an alternative to the DNACPR. The UFTO will be filled in on all patients, and encourages the documentation of treatment decisions including resuscitation. We hypothesise that it will standardise physicians approach to resuscitation while respecting clinical judgement and patient choice. |
| Primary objective | To assess whether the UFTO improves the number of referrals in response to MEWS (modified early warning system) ≥ 3 in those patients who are not for resuscitation. |
| Secondary objective (s) | We will assess, along with legal, health economic and ethical implications, whether the form:   - Improves care for those not for resuscitation as measured by referral to specialities and other escalating care (e.g. HDU / ICU). - Reduces the number of patients who remain inappropriately for resuscitation. - Improves understanding in all groups about the appropriate implications of the decision not to resuscitate. - Creates a positive framework for discussions of treatment options with patients and their families   . |
| Study Design | Before and after study |
| Study Endpoints | Discharge from hospital, or transfer to another ward |
| Sample Size | 108 patients who are not for resuscitation in each group |
| Summary of eligibility criteria | All patients over 18 years of age, excluding those for palliative care on admission or with an admission of less then 24 hrs |
| Investigational medicinal product and dosage | No medicinal product included |
| Active comparator product(s) | DNACPR versus UFTO |
| Procedures: Screening & enrolment | All patients admitted to selected clinical areas are eligible |
| End of Study | Patient discharge or transfer to another ward. 30 day mortality will be assessed. |

**AMENDMENT TO PROTOCOL- NEW DATASET**

Following initial analysis of data from this study it was found that EWS scores greater than 3 did not occur as frequently as had been found in the preliminary data, therefore there was no statistical significance in these results. The collection of an additional dataset was then proposed and ethics approval obtained for an amendment to allow new data to be obtained using the IHI Global Trigger Tool. This tool was not in widespread use in the UK when the initial study was planned.

**Aim**

To assess rates of harm, as measured by the IHI Global Trigger Tool, in all patients ‘not for resuscitation’ during both the DNAR periods and following the introduction of the UFTO and to assess whether the UFTO was associated with reduced rates of harm in those ‘not for resuscitation’.

**Endpoint**

The primary endpoint was rate of harms per 1000 patient bed days as determined by the IHI Global Trigger Tool methodology. This was assessed in all patients ‘not for resuscitation’ in both the DNAR and UFTO period. The rate of harms per 100 patient admissions was also calculated within each patient group.

Since this was not our initial end point, a more stringent criteria of 0.02 will be considered statistically significant.

**Contemporaneous case controls**

Additional analysis were carried out on two contemporaneous case control groups.

1. A selection of patients on the studied wards who remained for resuscitation during the same period.
2. Those ‘not for resuscitation’ on wards where the intervention, the UFTO was not introduced during the same period.

**Statistical Analysis**

The primary endpoint was the rate of harms per 1000 patient bed days in those patients ‘not for resuscitation’, calculated separately for the group of patients with a DNACPR order and those receiving UFTO. The rate of harms per 100 patient admissions was also calculated within each patient group. The UFTO and DNACPR groups were compared by calculating the absolute rate difference between the groups with a corresponding 95% confidence interval. A stratified analysis was then performed by calculating the rate differences within each ward group. Patient characteristics were compared between groups using the Fisher’s Exact test for all categorical variables and the Mann-Whitney test for all continuous variables except age, for which an independent samples t-test was used. This was because all continuous variables except age had non-normal distributions.

The frequency distribution of the type of harms, and the severity and preventability of harms was tabulated for each group. The chi-squared test for trend was utilized where possible to statistically compare between the groups. However, in the case of tables with low expected counts, Fisher’s Exact tests were used.

Difference in proportions were calculated to compare the number of harms contributing to patient death and the number of harms preventable at any level between groups, with corresponding 95% confidence intervals calculated using a recommended method (Newcombe’s method) [1]. The same method was used to compare discussion rates, EWS response and mortality between groups.

A Poisson regression model was fitted to the number of harms data to evaluate the effect of group (UFTO/NFR or DNACPR) on number of harms after adjusting for possible confounders. For the first model, only the group variable was included as an explanatory variable in the model; and then ward was also added; and finally, a model was fitted including all covariates of interest: ward, gender, Charlson co-morbidity score, MEWS score and age at admission. For all models, a log-transformed offset term was included for hospital length of stay, to adjust for differences in periods of observation across patients.

As a sensitivity analysis, negative-binomial regression models were also fitted to account for any over-dispersion in the data. As before, a log-transformed offset term was included for hospital length of stay, to adjust for differences in periods of observation across patients.

To determine the effect of including palliative care patients in the analysis, exactly the same statistical methods were employed as above but with the addition of the palliative care patients.

R software version 2.15.0 [2] was used for most analyses, except SPSS software version 18 [3] was used for data manipulation and to calculate summary statistics and p-values when comparing patient characteristics between groups.

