***Secondary objectives***

We will assess, along with legal, health economic and ethical implications, whether the form:

Increases care for those documented as not for resuscitation, but for active treatment (defined as active treatment in the UFTO group, and no statement of ceiling of care in the DNACPR group). This will be measured by:

- 1. review by other specialities
  2. referral and acceptance to escalating care (e.g. HDU / ICU)
  3. radiological investigation
  4. prescription of “expensive” drugs (where “expensive” is from a predefined list supplied by pharmacy);

Specifically, we will assess whether introduction of the UFTO alters *in isolation and as a composite endpoint* the above mentioned factors.

- Alters length of stay or in-hospital mortality;
- Improves care towards the end of life by encouraging advance care planning;
- Reduces the number of patients who remain inappropriately for resuscitation as judged by total numbers;
- Improves understanding in all groups about the appropriate implications of the decision not to resuscitate, as assessed by qualitative interviews and questionnaires and ethnographic research;
- Creates a positive framework for discussions of treatment options with patients and their families, as assessed by qualitative interviews and questionnaires and ethnographic research;
- To map the current decision-making processes around resuscitation: both explicit and implicit factors, across all groups
- To assess all groups’ attitudes and feelings about the old DNACPR and new UFTO, and compare their differing perspectives
- To assess the ethical problems faced by professional staff in using the conventional DNACPR form and the new UFTO
- To establish what elements of experience from each differing perspective are felt to be associated with the question of resuscitation in order to recognise the ways it has meaning in terms of the overall expectations of care
- To learn from outcome data of the above to inform an optimised approach to resuscitation decisions framed by the UFTO.

Trial Design

EVALUATION OF THE UFTO

The form to be trialled has been developed as described in the introduction

Study Summary

A before and after study will be carried out on the respiratory and general medicine ward, and General Medical/endocrinology and elderly care ward (G4) at the West Suffolk Hospital. Patients under 18 or for palliative care only on admission or who have an admission of less the 24 hours will be excluded.

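### The comparison attached to the primary harm endpoint is a crude rate difference with a 95% interval; the planned adjusted model has no rank above it, and the interval does not match the 0.02 criterion.

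*Protocol*

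**What the plan says.** All references are to the Protocol.

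- **Design (Trial Design, Study Summary).** "A before and after study will be carried out on the respiratory and general medicine ward" and on a second ward. Allocation is by period, not by randomisation.
- **Reason for the amendment (New Dataset).** High early-warning scores were rarer than expected, "therefore there was no statistical significance in these results", and a new dataset was then proposed.
- **Endpoint and level (amendment, Endpoint).** "The primary endpoint was rate of harms per 1000 patient bed days as determined by the IHI Global Trigger Tool methodology". The level follows: "Since this was not our initial end point, a more stringent criteria of 0.02 will be considered statistically significant".
- **Comparison (amendment, Statistical Analysis).** "The UFTO and DNACPR groups were compared by calculating the absolute rate difference between the groups with a corresponding 95% confidence interval". Rate differences within each ward group come next.
- **Models (same section).** There are three Poisson models with a log length-of-stay offset. "For the first model, only the group variable was included"; ward is then added, and finally gender, Charlson score, MEWS and age. Negative-binomial models are labelled a sensitivity analysis, and their number is not given.
- **Other results.** "The rate of harms per 100 patient admissions was also calculated within each patient group". All methods are repeated with palliative care patients to show the effect of including them. Two contemporaneous control groups are described as additional analysis; one consists of patients not for resuscitation on wards without the form.

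The section does not use the term primary analysis, and no sentence says which of these results is held to 0.02.

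**The concern.** A crude contrast between two periods mixes the effect of the form with any difference in who was in the group. The protocol gives its own reason to expect such a difference: under Trial Aims it hypothesises that fewer patients will inappropriately stay for resuscitation. If so, the form changes membership of the group being analysed. Should the added patients be less ill, the crude harm rate falls with no benefit from the form; should they be more ill, a benefit is hidden.

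The plan recognises confounding, since it fits an adjusted model, but does not say that this model decides. If the crude and adjusted results disagree, nothing in the text settles which is the finding. The endpoint was adopted after the first one gave no significant result, and 0.02 is the stated safeguard for that change. The safeguard is weak if it is tied to no single analysis and if the only stated interval belongs to a different level.

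**Working it through.** **1. The protocol's own figure.** The 108 per group belongs to the original early-warning endpoint (two-sided Fisher test, 5%, 80% power, 20-point difference). The control proportion is not given. Assuming 60% against 40%, the continuity-corrected size is 107 and exact Fisher power at 108 is 0.802; 50% against 30% gives 0.822 and 30% against 10% gives 0.952. The figure reproduces, but no size or power is stated for the harm endpoint. Below, 108 serves only as a plausible group size.

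**2. Interval against level.** Sidedness is not stated; two-sided is assumed.

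- 95% interval: z = 1.960, which matches 0.05.
- 98% interval: z = 2.326, which matches 0.02.
- Ratio of widths: 2.326 / 1.960 = 1.187.

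For any p-value between 0.02 and 0.05, the stated interval excludes zero while the stated criterion is not met.

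**3. Case mix and the crude ratio.** Assume the harm rate multiplies by r per Charlson point, the UFTO group averages d points lower, and the form has no effect. The crude rate ratio is then r^(-d). These inputs are not in the protocol.

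- r = 1.05, d = 1: 1/1.05 = 0.95
- r = 1.10, d = 1: 1/1.10 = 0.91
- r = 1.20, d = 1: 1/1.20 = 0.83

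The direction reverses if the UFTO group is the sicker one.

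**4. Unranked results.** The whole-group results on the primary endpoint without a secondary label are the crude difference and three Poisson models, so four.

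- Fully correlated: 2%.
- Independent: 1 − 0.98^4 = 0.078.

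The four use the same harms in the same patients. The group-only Poisson model with its offset is nearly the crude contrast again. The truth therefore lies below 7.8%, provided each test holds its own level.

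**5. Does each test hold its level?** This was simulated with no effect, 800 runs per scenario. Assumptions, none from the protocol:

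- 108 per group, about 0.05 harms per bed day;
- length of stay log-normal, median 9 days, log-SD 0.8;
- log rate ratios of 0.3 per SD of Charlson, 0.15 per SD of MEWS and 0.2 for ward;
- gamma over-dispersion phi, and a Charlson imbalance between periods in SD units;
- Poisson variance for the crude difference; moment-estimated dispersion for the negative-binomial model.

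Percentage of runs with p ≤ 0.02:

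| Imbalance | phi | Crude difference | Adjusted Poisson | Adjusted negative-binomial |
|---|---|---|---|---|
| 0 | 0 | 3.4 | 2.1 | 2.0 |
| 0 | 0.5 | 7.6 | 6.1 | 2.4 |
| 0 | 1.0 | 15.6 | 13.1 | 3.6 |
| 0.25 | 0 | 4.8 | 1.9 | 1.6 |
| 0.25 | 0.5 | 8.2 | 5.1 | 1.8 |
| 0.25 | 1.0 | 17.0 | 14.6 | 3.5 |
| 0.5 | 0 | 11.4 | 1.8 | 1.8 |
| 0.5 | 0.5 | 19.6 | 8.4 | 3.6 |

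The scenario with imbalance 0.5 and phi 1.0 did not finish. Monte Carlo error is √(p(1−p)/800), about 0.5 points at 2% and 1.4 points at 20%.

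Two mechanisms are visible. Imbalance inflates the crude result, and adjustment removes that. Over-dispersion inflates both the crude and the Poisson results, and only the negative-binomial variance largely removes it. The adjusted models are flattered here because every confounder in the simulation is measured and modelled.

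**The case against.** **The plan already deals with confounding.** This is partly true. It has adjusted models, ward-specific differences, baseline comparisons and two contemporaneous control groups. A reader might infer that confounding is ignored; the text does not support that. What is missing is a rank for the adjusted model.

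**If the crude difference is primary, 0.02 belongs to it and there is no multiplicity.** That is a fair reading, because it is the comparison attached to the primary endpoint. It disposes of most of the multiplicity, but the decisive result is then the one most exposed to case mix, and its stated interval still does not fit 0.02.

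**Many more results could be held to 0.02.** A reader might count eight (two rates, three Poisson models, three negative-binomial models) or sixteen with palliative patients, and quote 1 − 0.98^8 = 15%. The protocol does not support this. The negative-binomial models are labelled sensitivity and their number is not stated. The palliative repeat has its own stated purpose, harms per 100 admissions is not the primary rate, and the results are far from independent.

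**Ranking of models belongs in an analysis plan, which is not shown.** This would count if the protocol were silent. The amendment instead has its own statistical section fixing models, covariates, offset and interval level, and the 95% against 0.02 conflict is in what it states.

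**Adjustment does not cure the design.** This stands. Listed covariates remove neither secular change nor all selection into the group.

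**Conclusion.** The point holds in a limited form. The comparison attached to the primary harm endpoint is unadjusted in a non-randomised before-and-after study. No sentence puts the planned adjusted model above it, and its 95% interval cannot be read against 0.02. The interval mismatch is certain if 0.02 is two-sided.

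The size of the rest depends on assumptions. Multiplicity from the four unranked results is modest: above 2% and below 7.8% if each test holds its level. Confounding and over-dispersion could matter more. In the scenarios run, the crude difference gave 3.4% to 19.6% false positives at 0.02, adjusted Poisson 1.8% to 14.6% and adjusted negative-binomial 1.6% to 3.6%. These figures show the mechanisms; they do not estimate this trial's error.

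A reader might go on to infer that any reduction in harms seen here is an artefact. The protocol gives no harm data and no direction of imbalance, so that does not follow. The point merits correction, but it does not invalidate the study.

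**What to change.** - **Name one decisive analysis:** the fully adjusted model already listed, with ward, gender, age, Charlson score and admission MEWS, the log length-of-stay offset, and palliative patients excluded. Say explicitly that MEWS is the baseline value recorded under Data Collection, because a score from later in the stay could reflect care given.
- **Settle the variance:** use the negative-binomial model already planned, or a Poisson model with robust variance (the latter was not simulated above).
- **Match the level:** judge this result at two-sided 0.02 and report a 98% interval.
- **Rank the rest:** label the crude rate difference, ward-specific differences and other models as supportive.
- **State the timing:** say whether this choice was made before the harm results were seen. Statistical Analysis is in the past tense and describes observed distributions, so some data had been examined. If the choice came later, say so; naming a model then cannot fully restore prespecification.
- **State the limit:** acknowledge that adjustment does not remove secular change or all selection into the group, and read the result alongside the control group from wards without the form.

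Cost: the covariates are already collected and both model families are already in the plan. The headline changes from an absolute difference to a rate ratio, and its 98% interval is about 1.19 times as wide as a 95% one (on the log scale), and wider again where over-dispersion is present. The absolute difference remains available as a supportive result.

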**The IHI Global Trigger Tool Methodology**

The IHI Global Trigger Tool (IHI GTT) was developed by the Institute for Healthcare Improvement (IHI) to identify “harm” which has occurred to patients in hospital. A UK version has become widely used since 2009. The GTT has a series of objective “triggers”  - for example a fall, or a lack of early or EWS requiring response.

Primary review will be conducted in accordance with the IHI guidelines in a standardised fashion (outlined in a Standard Operating Procedure in an appendix to this protocol) and in 20 minutes or less, by one of two reviewers. Primary reviewers, one research nurse and one junior physician, will review case notes in a random order. Using predetermined selected modules of the UK Global Trigger Tool, any of the 29 triggers met (not just those which they think might be associated with a harm) will be recorded into a filemaker database. Primary reviewers will write a paragraph or two describing each trigger event, no determination of the presence of harm will be made at this stage. Multiple triggers can be recorded for an individual patient. This first 20 sets of notes will be reviewed by both primary reviewers to establish inter-rater reliability and standardization of the review process.

Secondary Consultant physician reviewers will then review the information prepared by primary reviewers. The secondary reviewers will be blinded to demographics, dates of admission and discharge, ward, and whether the patient was in the DNAR or UFTO group.

To maximise concordance, focus specifically on what occurred during the admission, and to minimise confounding, some additional criteria not included in the standardised GTT were predetermined before rating of harm, again outlined in more detail in the SOP for GTT review in an appendix to this protocol.

Secondary reviewers will independently assess each blinded record, determining the presence of a harm associated with a trigger. Where a harm is present, the severity and preventibility will also be recorded. Severity will be classified using the index of the National Coordinating Council for Medication Error Reporting and Prevention (NCC MERP) This gives five categories of harm- category E: temporary harms requiring intervention; category F: temporary harms

requiring initial or prolonged hospitalization; category G: permanent harms; category H:life- threatening harms; and category I :harms causing or contributing to death.

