A Likert scale with scores ranging from 1 for “definitely not preventable” to 4 for “definitely preventable” will be used to evaluate preventability

Cases in which physician reviewers disagree will be discussed, and consensus reached; where this is not possible, a third opinion will be obtained. Inter-rater reliability on the presence of aharm will be calculated from pre-discussion ratings.

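### One test rule covers type, severity and preventability of harm: it gives no sound test for a well-filled harm-type table, and in sparse tables it drops the order of the two graded scales

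*Protocol*

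**What the plan says.** The relevant text is in the Protocol amendment, section Statistical Analysis. It first names three tables: "The frequency distribution of the type of harms, and the severity and preventability of harms was tabulated for each group". It then gives a default test: "The chi-squared test for trend was utilized where possible to statistically compare between the groups". One exception follows: "However, in the case of tables with low expected counts, Fisher’s Exact tests were used". No other test is named for these tables. The next paragraph of that section takes two contrasts separately, harms contributing to death and harms preventable at any level, as differences in proportions with Newcombe 95% confidence intervals.

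The section on the IHI Global Trigger Tool Methodology fixes two of the three scales. Severity is graded E to I: "This gives five categories of harm- category E: temporary harms requiring intervention; category F: temporary harms", and so on up to harms causing or contributing to death. Preventability is graded 1 to 4: "A Likert scale with scores ranging from 1 for “definitely not preventable” to 4 for “definitely preventable” will be used to evaluate preventability". No list of harm types is given, and no order among them.

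The Statistical Analysis section ends by repeating the same methods with palliative care patients added, so the rule applies there as well.

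**The concern.** A chi-squared test for trend gives each category a score and asks whether the split between groups drifts along those scores. That is sensible for E to I or 1 to 4. For type of harm there is nothing to score. If the trend test is used there, the result depends on which type is listed first, second and so on, and an arbitrary listing could produce either a spurious difference or a missed one.

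The sparse-table rule has a smaller weakness. With five severity grades and four preventability grades, low counts in the rarer grades are plausible. Fisher's exact test then replaces the trend test and asks a different question: whether the distributions differ in any way, not whether one group's harms are graded higher. Cell counts alone would decide which question is answered.

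At stake is how the nature and severity of harms in the DNACPR and UFTO groups are described, not the trial's main comparison.

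**Working it through.** **Step 1. What the text fixes for each table.** The Protocol states no harm counts, power or significance level for these tables, so there is no figure to reproduce.

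| Table | Order stated? | Adequate counts | Low expected counts |
|---|---|---|---|
| Type | No | Trend test if read literally; no test named if *where possible* means ordered tables only | Fisher: suitable |
| Severity, E to I | Yes | Trend test: suitable | Fisher: valid, ignores order |
| Preventability, 1 to 4 | Yes | Trend test: suitable | Fisher: valid, ignores order |

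The first cell is deficient on either reading. The two sparse cells for ordered scales are inefficient.

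**Step 2. Trend test on unordered categories (assumed data).** Take five harm types with counts a = 14, 10, 8, 12, 6 in one group (50 harms) and b = 6, 12, 10, 5, 10 in the other (43 harms). Category totals are n = 20, 22, 18, 17, 16, with N = 93 and p = 50/93 = 0.5376. The smallest expected count is 16 × 43/93 = 7.4, which is above the usual threshold of 5 for calling a count low (an assumption, since the Protocol sets no threshold).

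With scores s, the trend test uses
- T = Σ s·a − p·Σ s·n
- V = p(1 − p)·[Σ n·s² − (Σ n·s)²/N]
- X² = T²/V on 1 degree of freedom.

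*Listing 1*, scores 3, 2, 1, 4, 0:
- Σ s·a = 118 and Σ s·n = 190, so T = 118 − 190 × 50/93 = 15.85.
- Σ n·s² = 558, so V = 0.2486 × (558 − 190²/93) = 42.2.
- X² = 15.85²/42.2 = 5.95, p = 0.015.

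*Listing 2*, scores 0, 3, 2, 4, 1:
- Σ s·a = 100 and Σ s·n = 186, so T = 100 − 186 × 50/93 = 0, p = 1.00.

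The data are the same and only the listing differs. Over all 120 listings p runs from 0.015 to 1.00, with median 0.36. It is below 0.05 in 20% of listings and below 0.02 in 6.7%. (The Endpoint section sets 0.02 for the new endpoint: "Since this was not our initial end point, a more stringent criteria of 0.02 will be considered statistically significant". It sets no level for these tables.) Pearson's chi-squared on 4 degrees of freedom gives p = 0.136 whatever the listing.

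A second assumed table, 20, 10, 15, 5, 10 v 10, 18, 8, 14, 10 (60 harms per group), gives trend p-values from 0.0007 to 1.0 against a Pearson value of 0.017. There the trend test can miss a difference that the general test detects.

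**Step 3. Fisher's exact test on a sparse ordered table (assumed data).** Five ordered grades with probabilities 35, 35, 10, 10 and 10% in one group and a proportional-odds shift in the other; 2,000 simulated tables per scenario, 499 Monte Carlo draws per table, nominal level 0.05. With no effect, Fisher rejected in 0.041 to 0.051 of tables, so it holds its level. Power of Fisher v a permutation trend test:

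| Harms per group | Odds ratio 2 | Odds ratio 3 |
|---|---|---|
| 20 | 14% v 16% | 28% v 35% |
| 30 | 17% v 24% | 41% v 50% |
| 50 | 29% v 39% | 64% v 76% |

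The loss is about 2 to 12 percentage points. It is not a bound: the gap widens if harms are spread more evenly over the grades and narrows if they pile up in the mildest grade. Steps 2 and 3 both treat harms as independent.

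**The case against.** The best defence rests on *where possible*. A trend test is meaningful only for ordered categories, so a statistician may read the phrase as confining it to severity and preventability. The following sentence adds a condition about low counts and need not define the earlier phrase. Nothing in the Protocol says that a trend test was in fact run on harm type. This stands, and the defect is partly one of wording. But the only exception written down is "in the case of tables with low expected counts"; scale is never mentioned. On the generous reading, a harm-type table with adequate counts has no test at all, so the text needs correcting either way.

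A harm-type table might also have many thin categories, since 29 triggers are screened, and would then go to Fisher's exact test, which suits it. That is possible, but the number of types is not stated, so it cannot be relied on.

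A reader might infer that both tests are wrong for their scales. The documents do not support that. The trend test suits severity and preventability, Fisher's exact test suits a sparse type table, and on a sparse ordered table Fisher keeps its error rate and only loses power.

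It can also be said that assigning tests to tables belongs in a statistical analysis plan. Often it does, but here the Protocol itself names the tests and the trigger for switching.

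Finally, the counts used above are invented. They show how the tests behave and measure nothing in this trial.

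**Conclusion.** The point holds as a minor correction. As written, the rule either applies a trend test to categories with no stated order or names no test for harm type when counts are adequate. For sparse severity and preventability tables, the fallback is valid but discards the order.

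A p-value for harm type from a trend test would be arbitrary: 0.015 to 1.00 in one assumed table, 0.0007 to 1.0 in another. The power loss from Fisher's exact test was about 2 to 12 percentage points in the assumed scenarios. None of these figures is a trial result.

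The effect is confined to secondary tabulations. The primary rate difference with its 95% confidence interval, the Poisson and negative-binomial models, and the Newcombe intervals for fatal and preventable harms do not depend on it. No stated sample size or significance level changes. It would go too far to conclude that a meaningless p-value has been produced: the text permits one but does not show that one was calculated.

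**What to change.** Replace the single rule by a test named for each table:

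- **Type of harm:** Pearson chi-squared test, or Fisher's exact test when expected counts are low.
- **Severity (E to I) and preventability (1 to 4):** chi-squared test for trend with the category scores stated, or an exact (permutation) trend test when expected counts are low.
- State what counts as a low expected count, and apply the same rule to the analysis that adds palliative care patients.

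The cost is a sentence or two of text and re-running a few secondary tables. No new data are needed.
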